### Exploring outcomes

At baseline and after 6 weeks of treatment, fecal samples will be collected and stored at – 80 °C for unified testing. The experimenter will extract total DNA from the fecal samples and perform 16S rRNA sequencing. Reads will be processed to generate an operational taxonomic unit (OTU) table at 97% granularity. Through OTU analysis, the detected α-diversity and β-diversity of the fecal microbiome will be detected, and then the LEfSe analysis will be used to compare and analyze the data to identify species with significant differences in abundance between groups.

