Tongjiang (TJ) methodology is used in TCM to treat functional gastrointestinal diseases. TJ literally means unobstructed and descent, and the main goals of TJ methodology in TCM are to regulate visceral dysfunction, adjust the imbalance between internal and external energies, restore the physiological functions of the viscera, and revitalize the mind, spirit, and body for a holistic well-being balance. Herbal granules based on TJ methodology can help regulate cell-to-cell tonic equilibrium and improve the overall Qi and food passing unimpeded through the entire gastrointestinal tract. Prior to this trail, we have performed an RCT study on the efficacy of TJ granule to improve the quality of the results and to provide estimates for further sample size calculation. The results showed that TJ granule could improve the symptoms which included heartburn, chest pain, acid or bitter tastes in mouth, and nausea. On the quality of life, it could also improve the domains of physical functioning and general health, and no adverse event was found [23].

For most common patients presented with NERD [17], we will use TCM granules based on the TJ methodology in cooperation with PPI step-down therapy to treat NERD. We designed this rigorous multicenter, double-blinded, RCT using TJ methodology granules with PPI step-down therapy for NERD patients with regard to NERD-related symptoms and symptom distress, to explore its therapeutic efficiency, measure recurrence rate, understand the mechanisms of the therapy, and estimate PPI withdrawal rate.

We aimed to independently examine the efficiency and safety of TJ methodology granules combined along with PPI step-down therapy for NERD patients with regard to NERD-related symptoms and symptom distress. The primary objective is to develop a new therapy for the treatment of NERD, to obtain high-level evidence-based medical evidence. The secondary objective is to evaluate the advantages of the new therapy, hoping to solve the problems of side effects and dependence caused by long-term use of PPIs. The last objective is to explore some of the mechanisms based on observations of the changes in patients’ gut microbiota.

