We regard this trial with upmost importance due to the facts that 20–30% of NERD patients do not respond to PPI treatment [45] and that the long-term use of PPIs produces dependence and negative side effects [46, 47]. With the cooperation of TCM granules and PPI step-down therapy, it can synergistically adjust the holistic internal and external energy of NERD patients. On the premise of relieving symptoms, gradually reduce the dosage of acid suppressive drugs every 2 weeks to withdraw. It can provide a solution to the problem of NERD patients not responding to PPIs and reduce the side effects caused by long-term use of PPIs. Experiments had proved of the effect of granules based on TJ methodology on increasing the level of plasma motilin, reducing the level of gastric acid, and promoting the gastric emptying. The acute toxicity experiment showed that there was no toxic reaction in mice [23].

This trial will use VAS for heartburn and regurgitation, major and minor symptoms scales, SF-36, PRO, SAS, SDS, GERD–HRQL, TCM syndromes scales, and symptom recurrence rate to measure physiological and psychological outcomes to comprehensively evaluate the changes imposed by this therapy for the participants before, during, and after treatment and the PPI withdrawal rate, in order to provide high-level medical evidence for the TCM treatment of NERD and to form a new therapy regimen for NERD. For patients with long-term use of PPIs that are unable to withdraw, the advantages of the new therapy and the mechanisms related to gut microbiota will be evaluated. This trial is expected to solve the side effects and dependence caused by long-term use of PPIs and compare the gut microbiota diversity of healthy volunteers and NERD patients before and after treatment to prepare for the next step of exploring the underlying mechanism of the disease. The results of this trial will help to improve the quality of evidence of TCM studies and the clinical efficacy of NERD treatments, reduce dependence on PPIs, and improve the quality of life of patients, ideally yielding good social benefits.

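### The microbiota analysis names only a between-group LEfSe comparison and states no use of each participant's baseline stool sample; adjusting for it would cost almost nothing and could add precision

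*Protocol article*

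**What the plan says.** Four places in the protocol article bear on this.

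- **Background, objectives.** The last of the three objectives is to "explore some of the mechanisms based on observations of the changes in patients’ gut microbiota".
- **Exploring outcomes, sampling.** "At baseline and after 6 weeks of treatment, fecal samples will be collected". The design therefore yields a pair of samples per participant.
- **Exploring outcomes, analysis.** After 16S sequencing and OTU construction, α- and β-diversity are derived, with no test named. For taxa, the stated step is "then the LEfSe analysis will be used to compare and analyze the data to identify species with significant differences in abundance between groups". The text does not say which time point is compared, whether the groups are arms, time points or something else, or how the baseline sample enters.
- **Discussion.** The trial is also expected to "compare the gut microbiota diversity of healthy volunteers and NERD patients before and after treatment". This concerns diversity rather than the abundance of individual taxa, and no test is given.

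The Statistical analysis section lists the Wilcoxon signed-rank test among its options for non-normal continuous variables. It does not link that test to the microbiota data.

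**The concern.** The objective is about change and the sampling is paired, but the one abundance method named is a comparison of independent groups. LEfSe screens taxa with rank tests that treat every sample as a separate unit, so a participant's own starting level plays no part.

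The gut microbiota may differ more between people than it shifts within a person over six weeks. Where it does, the baseline sample is the natural means of removing that variation. An analysis that ignores it answers the mechanism objective with less precision than the collected data allow.

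A second risk comes from the open wording. Someone running the screen could load all samples labelled by arm, so that each participant counts twice.

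Both points hold for a single taxon. They are separate from the question of how many taxa are tested.

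**Working it through.** **The plan's own figure.** The protocol gives no power or precision figure for the microbiota analysis. Its total of 174 can be reproduced: per arm, (0.9 × 0.1 + 0.7 × 0.3) × (1.960 + 0.842)² / (0.20 − 0.02)² = 72.67, and 72.67 × 1.2 = 87.2. The point here does not depend on it. It is used only to set the number of participants.

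**Inputs**
- 87 per arm and 20% attrition (Sample size estimation): 87 × 0.8 = 69.6, taken as 70 per arm. This assumes every completer gives both samples.
- Two-sided 0.05 (Statistical analysis).
- Assumed, not in the document: one taxon on a transformed, roughly normal scale; a week-6 shift of 0.4 SD between arms; and correlation r of 0.3, 0.5 or 0.7 between a participant's baseline and week-6 values, with r = 0 as the limiting case.

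**Reading A: arms compared at week 6 only.** Randomization balances baseline in expectation, so the test is valid. In a simulation of the rank test with 87 per arm, the false-positive rate was 4.4–5.8% across r from 0 to 0.9.

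The cost is precision. Adjusting for baseline multiplies the residual variance by (1 − r²), so its sample-size equivalent is 1/(1 − r²):
- r = 0.3: 1/0.91 = 1.10
- r = 0.5: 1/0.75 = 1.33
- r = 0.7: 1/0.51 = 1.96
- r = 0: 1.00

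In power terms, the unadjusted signal is 0.4 × √(70/2) = 2.366, and power is Φ(2.366 − 1.960) = 66%. With adjustment, the signal is divided by √(1 − r²).

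| r | Adjusted signal | Power, adjusted (formula) | Power, adjusted (simulation) | Power, week-6 rank test (simulation) |
|---|---|---|---|---|
| 0.3 | 2.481 | 70% | 69% | 64% |
| 0.5 | 2.733 | 78% | 77% | 62% |
| 0.7 | 3.314 | 91% | 91% | 63% |

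A second set of inputs (87 per arm, 0.3 SD) shows the same pattern: 51% unadjusted at every r, against 55%, 63% and 79% adjusted at r = 0.3, 0.5 and 0.7.

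A simple change score is not an equivalent remedy. Its residual variance is 2(1 − r), which exceeds 1 when r < 0.5. At 0.3 SD and r = 0.3 its power is 39%, below the 51% of the week-6 comparison.

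**Reading B: both samples of each participant entered by arm as independent.** The true variance of an arm mean is then (1 + r) times what the test assumes, so the nominal cut-off of 1.960 acts as 1.960/√(1 + r):
- r = 0.3: 1.719, false-positive rate 8.6% (simulated 8.0–8.4%)
- r = 0.5: 1.600, false-positive rate 11.0% (simulated 10.6–10.9%)
- r = 0.7: 1.503, false-positive rate 13.3% (simulated 12.9–13.2%)

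The effect is also halved, because the baseline half of the samples carries no treatment difference. Simulated power at 0.4 SD and 70 per arm is 38–39%.

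**Reading C: baseline against week 6 within an arm, unpaired.** Here the test is too cautious. With 87 participants the simulated false-positive rate is 2.2%, 0.5% and 0.2% at r = 0.3, 0.5 and 0.7. Power at 0.3 SD is 44–49%, against 64–93% for the paired test.

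**The case against.** The strongest reply is that this is one condensed sentence about an exploratory outcome in a journal article, and that how baseline enters may be settled in a full protocol or analysis plan that is not shown. Silence is not exclusion: the Discussion foresees a comparison of diversity before and after treatment, and the general statistics section lists a paired rank test. This stands in part. A reader might infer that the plan forgoes any paired use of the baseline samples. The document does not support that.

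A reader might also infer that a week-6 comparison fails to test the treatment effect on change. It does not fail. Between randomized arms it is a valid test, and it beats a change score when r < 0.5. What is lost is precision only.

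A third tempting inference is that paired samples will be counted as independent. No section says so, and the 8–13% figure applies only if that were done.

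Finally, the gain rests on assumed values. At r = 0.3 it is modest, and part of the simulated step from about 63% to 69% comes from setting a rank test against a parametric model on normal data. Like for like it is 66% to 70%.

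What remains is that the article does choose a tool and a contrast, and that choice has no place for a participant's baseline. The signed-rank test does not fill the gap, since within one arm it cannot compare change between arms. The Discussion's before-and-after comparison covers diversity, not taxa.

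**Conclusion.** The point holds as a cheap improvement, not as an error that invalidates the analysis. The objective is change and the samples are paired, but the only named abundance analysis makes no stated use of the pairing.

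On the most natural reading (arms at week 6), the loss is equivalent to forgoing 1.10 to 1.96 times the sample size for r between 0.3 and 0.7, and there is no loss at r = 0. An inflated false-positive rate of about 8–13% per taxon is a conditional risk that the wording leaves open, not a stated plan.

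These sizes depend on the assumed correlation, an assumed 0.4 SD shift for the power figures, approximate normality after transformation, and stool from all completers. They apply per taxon, before any allowance for multiple taxa.

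Importance is low: the outcome is exploratory, and no primary or secondary result is affected.

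**What to change.** In Exploring outcomes:

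1. State that the between-arm comparison is baseline-adjusted. For each taxon, model week-6 transformed abundance on arm with that taxon's baseline value as covariate, and do the same for α-diversity. An equivalent baseline-adjusted differential-abundance model would serve as well.
2. Keep LEfSe as a descriptive display of week-6 samples by arm, and say that this is what "between groups" means there.
3. State that samples from the two time points are not pooled as independent observations.

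**Cost.** A paragraph of wording, slightly more analysis work, and a choice of transformation for sparse taxa with many zeros, best fixed before the sequencing data are seen. No additional samples, visits or participants are needed.

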### Data management and monitoring

We will use both written and electronic CRF. At each time point, participants will complete the CRF under the guidance of a TCM physician. The completed CRF will be entered into the Drug & Clinical Trial Data Management Platform (developed by the GCP center: http://www.xyedc.com/). The CRF data will be entered in duplicate by two trained TCM physicians. Electronic data will be permanently saved. After the study, the statisticians will be able to download the electronic data for analysis through the platform.

The Data Monitoring Committee (DMC) reviews some of the data in the form of interim analyses to make preliminary judgments about the efficacy and safety of the study drug. The DMC is responsible for ensuring the safety and benefit of the subjects, the integrity and credibility of the trial, and the timely and accurate feedback of study results to the relevant areas of clinical research. The monitoring plan foresees the conduction of a total of four monitoring visits from the point of selection of the first study patients to the end of the regular monitoring visits. After charting all adverse events reported during the study period, the incidence of adverse events will be determined.

### Statistical analysis

This trial will use intention-to-treat (ITT) analysis as the main method to evaluate the outcome results. To deal with missing outcome variables that remain to be recorded, the last record data will be carried over to the end or a multiple imputation method will be used.

Statistical analysis will be conducted using the SPSS 21.0 software. The significance level is established at 0.05, and the limits of the confidence interval are 95%. Descriptive analysis and categorical variables will be described in frequency tables and as percentages or composition ratios; continuous variables will be described in terms of means and standard deviations (SDs), or medians, lower quartiles (P25), upper quartiles (P75), minimum values, and maximum values. Comparative analyses between two groups will be performed for categorical variables using the chi-squared test, Fisher’s exact probability method, the Wilcoxon rank-sum test, or the CMH test. Continuous variables that conform to a normal distribution will be compares using a *t*-test (for homogeneity of variance between groups, with 0.05 as the test level; if the variance is heterogeneous, the Welch-Satterthwaite *t*-test will be used), while those that conform to a non-normal distribution will be compared using the Wilcoxon rank-sum test or the Wilcoxon signed-rank test. Hypothesis testing will use the two-sided test uniformly, and *P* ≤ 0.05 will be considered statistically significant.

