#### Dropout criteria

Decision to exit the trial himself/herselfLoss to follow-upPoor complianceDiagnosis with other TCM syndromes or an order to withdraw by the TCM physicians

For the occurrence of patients presented with the above situation, we will consider making a suspension. In cases of dropout, the reason should be explained. If there are baseline pharmacodynamic data, the last main therapeutic effect index can be transferred to the final results for statistical analysis, and the CRF should be retained.

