#### Intervention group

Based on the curative effect of treating NERD in clinical practice, we selected three kinds of TCM granules based on TJ methodology. According to the different TCM syndromes, participants with stagnation of liver and stomach-heat syndrome will be treated with Tongjiang (TJ) granule, those with spleen deficiency and dampness-heat syndrome will be treated with Jianpiqinghua (JQ) granule, and those with intermingled heat and cold syndrome will be treated with Wenpiqingwei (WQ) granule. These herbal granules are available from the Xiyuan Hospital as an in-hospital preparation. TCM granules are concentrated herbal particles obtained by the mean of spray drying the hot water extract of a mixture of raw herbs. TCM granules are extracted with water to make an aqueous extract or decoction used for treatment. Each bag of granules (approximately 20 g) will be dissolved in 200 ml water and taken twice a day, 1 h after meal. Participants in all three groups cooperated with PPI step-down therapy. From week 1 to week 2 of treatment, the dose of PPIs will be half of the original dose, once a day, taken before bedtime. The PPIs will be replaced with famotidine 20 mg from week 3 to week 4, taken before bedtime. From week 5 to week 6, acid-suppressive drugs will be withdrawn, and only TCM granules will be administered. There will be 6 weeks of treatment and 4 weeks of follow-up.

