### Cointerventions

One week prior to the start of treatment, patients will be required to stop their intake of other drugs related to TCM therapies of NERD; however, acid-suppressive drugs intake will remain unchanged. During the study period, patients will be forbidden to add any drugs other than study therapies without permission. During the 1–4 weeks of the treatment period, if the participant’s symptoms increase after the reduction of PPIs according to the study protocol and cannot be tolerated, participant can temporarily use almagate suspension or almagate chewable tablets and record the combined medication. During the treatment period of 5–6 weeks, if the participant is unable to tolerate the symptoms after stopping the acid suppressive drugs, participant will be terminated from the trial and recorded and will be treated with their original treatment therapy.

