### Primary outcomes

The primary outcomes are the VAS for heartburn and regurgitation and the major symptoms scale.The VAS is a line marked with 10 scales, with 0 points to 10 points at both ends. Zero points indicates no symptoms, and 10 points represents the most severe and unbearable symptoms. 0–2 is classified as “basic no symptoms,” 3–5 is classified as “mild,” 6–8 is classified as “moderate,” and 8–10 is classified as “severe” [27–29]. Patients will be given a VAS for regurgitation and heartburn daily through a diary card, and the average score of the two symptoms each week will be evaluated according to the content of the diary card. Participants were defined as responders if for at least 50% of weeks during the 6 weeks of the trial the weekly VAS score was reduced from baseline by ≥ 50%. We will calculate the percentage of responders. At the same time, the change in VAS score will be compared between groups.Major symptoms scale: For the main clinical symptoms of NERD, heartburn frequency, heartburn relief time, and regurgitation frequency, the scoring criteria are shown in Table 2.

**Table 2 Tab2:** Major symptoms scale

	Score		
	Mild (0)	Moderate (1)	Severe (2)
Symptom			
Heartburn frequency	1 day a week	2–3 days a week	4–7 days a week
Heartburn relief time	Relieve within 1h	Relieve within 1-3h	> 3 h does not relieve even all day
Regurgitation frequency	1 day a week	2–3 days a week	4–7 days a week

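### Participants terminated in weeks 5–6 for intolerable symptoms off acid suppression can still count as primary-outcome responders, because no rule scores them as non-response

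*Protocol article*

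**What the plan says.** All of this is in the Protocol article.

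- Intervention group sets the acid-suppression schedule, which applies to both arms: "From week 1 to week 2 of treatment, the dose of PPIs will be half of the original dose"; "The PPIs will be replaced with famotidine 20 mg from week 3 to week 4"; "From week 5 to week 6, acid-suppressive drugs will be withdrawn".
- Cointerventions allows almagate as needed in weeks 1–4. For weeks 5–6 it says that "if the participant is unable to tolerate the symptoms after stopping the acid suppressive drugs", the "participant will be terminated from the trial and recorded and will be treated with their original treatment therapy".
- Dropout criteria says that, where baseline data exist, "the last main therapeutic effect index can be transferred to the final results for statistical analysis".
- Statistical analysis makes intention-to-treat the main analysis and says of missing outcomes that "the last record data will be carried over to the end or a multiple imputation method will be used".
- Primary outcomes has a daily VAS diary averaged by week. A responder is a participant in whom "for at least 50% of weeks during the 6 weeks of the trial the weekly VAS score was reduced from baseline by" 50% or more.

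No section says how a termination for intolerable symptoms is scored in the responder analysis.

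**The concern.** Weeks 5–6 are the only treatment weeks without acid suppression, so they are where a participant shows whether symptoms stay controlled after withdrawal. A participant terminated there has a known, unfavourable result, and the data are missing because of the outcome itself. The stated rules do not use that information. They allow the gap to be filled from earlier weeks on half-dose PPI or famotidine, and they set a responder threshold that those earlier weeks can meet unaided. A recorded failure of the withdrawal phase can then enter a primary analysis as a success. That raises the responder rate in any arm where it happens, and distorts the comparison if it happens more in one arm than in the other.

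**Working it through.** The plan gives no termination rate and no figure for this situation, so there is nothing of its own to reproduce. The sample size of 174 is not at issue here. The check is whether the stated rules, applied together, can make a terminated participant a responder.

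**Inputs.** Threshold: 50% of 6 weeks = 3 weeks (Primary outcomes). Weeks on acid suppression: 1–4; weeks off: 5–6 (Intervention group). Termination: in weeks 5–6 (Cointerventions). Write w1 to w4 for weeks 1–4, each 1 if the VAS reduction is at least 50% and 0 otherwise. There are 2^4 = 16 patterns.

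**Case A: the last weekly score is week 4, carried into weeks 5 and 6.** Responder if w1 + w2 + w3 + w4 + 2·w4 ≥ 3.
- With w4 = 1 the sum is at least 1 + 2 = 3, so all 8 such patterns qualify. A good week 4 alone is enough.
- With w4 = 0 only (1,1,1,0) qualifies: 1 pattern.
- Total: 8 + 1 = 9 of 16.

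**Case B: a failing week-5 score is the last record and is carried to week 6.** Responder if w1 + w2 + w3 + w4 + 0 + 0 ≥ 3. That is 4 patterns with exactly three good weeks plus 1 with four: 5 of 16. Without carry-forward, counting weeks 5–6 as not responding gives the same 5.

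**Case C: termination scored as non-response.** 0 of 16.

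So, of the 9 patterns in case A, 5 qualify through the 3-of-6 rule alone and 9 − 5 = 4 are created by carry-forward.

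**From counts to probabilities.** The 16 patterns are not equally likely. As an assumption only, let each week respond independently with probability q. Case A has probability q + (1 − q)q³; case B has 4q³(1 − q) + q⁴.

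| q (assumed) | Case A | Case B | Case C |
|---|---|---|---|
| 0.3 | 0.32 | 0.08 | 0 |
| 0.5 | 0.56 | 0.31 | 0 |
| 0.7 | 0.80 | 0.65 | 0 |

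**Effect on an arm.** If a proportion t of an arm is terminated this way and a share s of these count as responders, that arm's responder rate is raised by t × s over case C. Taking s from 0.3 to 0.7 (assumed):
- t = 10%: 3 to 7 percentage points.
- t = 20% (about 17 of 87): 6 to 14 percentage points, or about 5 to 12 participants.

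**Effect on the comparison.** The difference, granules minus placebo, shifts by t_G·s_G − t_P·s_P. With similar s in both arms, more terminations on placebo make the shift negative (towards null if granules are better), more on granules make it positive (in favour of granules), and equal terminations cancel.

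**The case against.** The case on the other side is substantial, and several parts of it stand.

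- *Carry-forward is not fixed.* A reader might infer that terminated participants will have week-4, on-suppression scores carried forward. The documents do not say so. Statistical analysis offers carry-forward or multiple imputation, Dropout criteria only permits the transfer, and its list does not name terminations for intolerable symptoms. The VAS is kept daily and scheduled in weeks 5 and 6, so a failing week-5 score may be the last record. This stands, and it makes case A a possibility rather than the rule.
- *Carry-forward is not the main cause.* Five of the nine patterns come from the 3-of-6 rule. This stands: removing carry-forward alone would not solve the problem.
- *Multiple imputation is not shown to fail.* The article gives no imputation model, and a model can use the reason for stopping. This stands. The supportable statement is conditional: a model that ignores that reason could impute favourable values from the earlier weeks.
- *Other outcomes capture the failure.* The PPI withdrawal rate counts those no longer using PPIs at follow-up, and the primary outcomes also include VAS change and the major symptoms scale. This is true, but the withdrawal rate is secondary, and none of these settles who counts as a responder.
- *The detail may sit in the analysis plan.* An imputation model may. But the missing-data, dropout and responder rules are stated here, and the fault lies in how they combine.

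**Conclusion.** The point holds in limited form. The rules as written let a participant who failed the withdrawal phase count as a primary-outcome responder, and nothing in the document prevents it. The reach is 9 of 16 week 1–4 patterns if week 4 is the last score and is carried forward, and 5 of 16 if a failing week 5 is. These are counts of patterns, not probabilities.

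Responder rates are inflated wherever this happens. The direction of bias in the comparison depends on which arm terminates more, assuming that similar shares of the terminated count as responders. A reader might infer that the rule necessarily hides a benefit of granules, or costs the trial a definite amount of power. The document supports neither: it gives no termination rate in either arm, so both sign and size are unknown, and the percentage-point ranges in the working rest on assumed inputs.

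**What to change.** Change the analysis text only, before unblinding:

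- In Primary outcomes, state that termination for intolerable symptoms in weeks 5–6 is scored as non-response in the responder analysis, and repeat this in Dropout criteria and Statistical analysis so that the three sections agree.
- In Dropout criteria and Statistical analysis, remove carry-forward for the responder outcome.
- In Statistical analysis, name multiple imputation as the single primary method for data missing for other reasons, in place of the open choice.

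No new data are needed, because Cointerventions already requires the termination to be recorded. The 3-of-6-week threshold and the management of participants stay as they are. The cost is that responder rates in both arms become somewhat lower.
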